**Figure 3 F3:**
[figure not shown]
Participant timeline. The inclusion to the study includes an eligibility screening, the informed consent to participate and the qualitative purposeful sampling to intervention groups. Blue boxes mark quantitative and orange boxes qualitative assessment. The time points for data collection are: before the start of the intervention (T0), 2 weeks after the start (T1) and after the end of the intervention (T2).

All participants will be selected according to maximal variation sampling criteria to ensure a broad perspective on the research questions (40).

Maximal variation sampling will be applied pragmatically within the eligible pool available in the two participating facilities. The aim is to include a range of perspectives that are relevant for assessing feasibility and acceptability in a real-world long-term care setting. For residents, variation will be sought with regard to age, gender, and degree of mobility. For nursing staff, variation will be sought with regard to age, gender, and work experience. The exact number and socio-demographic composition of eligible residents and staff will depend on the participating facilities and will be documented during recruitment. Basic information on the available recruitment pool and the socio-demographic characteristics of included participants will be reported in the feasibility study.

Afterwards, residents will be assigned into two groups, aiming for an equal distribution of characteristics:
(1)“Residents completing a weekly VR session together with a nurse” and(2)“Residents conducting the sessions independently after initial instruction”.

In the joint sessions, nursing staff actively participate by watching a 360° video with the VR headset together with the resident. In addition, they may provide support if the resident encounters difficulties with the device or procedure. Including participants from two separate facilities as well as the variation between individual and joint sessions with nursing staff allows the exploration of contextual variability. The sample is adequate to inform adjustments to the study design and intervention for a subsequent RCT.

### Data collection

3.4

Data collection will be conducted on site at each pilot facility. Questionnaires will be administered at three time points: baseline (T0), two weeks after the start of the intervention (T1), and after completing the intervention (T2). Semi-structured interviews will be conducted post-intervention phase (T2) in a quiet, one-on-one setting to ensure privacy and minimise disturbances.

At baseline, basic socio-demographic and health-related characteristics will be collected to describe the sample and contextualize feasibility findings. For residents, these will include age, gender, duration of residence in the long-term care facility, degree of mobility, frequency of leaving the facility, relevant sensory limitations, previous experience with VR or similar digital technologies, and selected health information relevant to participation, such as contraindications to VR use and relevant physical or cognitive limitations. For nursing staff, baseline characteristics will include age, gender, professional role, years of professional experience, duration of employment in the facility, and previous experience with VR or similar digital technologies.

#### Qualitative data collection

3.4.1

At T2, semi-structured qualitative interviews (41) will be conducted with all participants to explore acceptance and feasibility, potential effects on residents and the nurse-patient-relationship and challenges of the intervention. The interview guide will include open-ended questions on the experience of using the VR headset, perceived facilitators and barriers, technical and organizational challenges, and the integration of the intervention into daily care routines. To connect the qualitative and quantitative strands, residents will also be asked about perceived changes in sleep, mood, wellbeing, loneliness or social connection, and trust in nursing staff. Nursing staff will be asked about their own experience of the intervention, perceived changes in residents during or after the sessions, feasibility within routine care, and perceived effects on interaction and relationship with residents. Pilot interviews will be conducted to ensure that the interview guideline is adjusted to participants and suitable for exploring the research questions. Minor adjustments may be made.

The interviewer is trained in qualitative research methods and supported by a methodological experienced team.

#### Quantitative data collection

3.4.2

In addition to interviews, residents will complete standardised questionnaires at T0, T1, and T2 to assess sleep quality, anxiety and depressive symptoms, psychological well-being, loneliness, and trust in nursing staff. All questionnaires will be verified onsite for completeness, and the data will be entered into a secure database.

Questionnaires used:

##### Pittsburgh sleep quality index (PSQI)

3.4.2.1

To evaluate sleep quality, the Pittsburgh Sleep Quality Index will be administered (42). 19 self-rated questions provide information about seven components commonly affected in people with sleeping disorders (subjective sleep quality, sleep latency, sleep duration, habitual sleep efficiency, sleep disturbances, use of sleeping medication and daytime dysfunction). Each component is scored from 0 to 3, yielding a global score of 0 to 21. Higher scores indicate poorer sleeping quality, with scores >5 suggesting clinically relevant sleep problems. The validated German version has demonstrated acceptable reliability (Cronbach's *α* = 0.75) and validity and has been widely tested in elderly patients (43).

##### The world health organisation-five well-being index (WHO-5)

3.4.2.2

The WHO-5 is a worldwide used questionnaire, consisting of five questions to evaluate subjective well-being in the past two weeks (44). Items are rated in a 6-point Likert scale from 0 (“at no time”) to 5 (“all of the time”), resulting in a raw total score of 0 to 25. For interpretation, scores are multiplied by four to yield a final score between 0 (the worst possible well-being) to 100 (the best possible well-being). A cut-off score of ≤50 is recommended to screen for depression.

The German version has shown excellent internal consistency (Cronbach's *α* = 0.92), strong construct validity, high acceptance and has been tested in older adults (45).

##### UCLA loneliness scale—six item version (ULS-6)

3.4.2.3

The ULS-6 is a validated short version of the UCLA Loneliness Scale (46). It consists of 6 items to evaluate perceived loneliness, rated on a 4-point Likert-scale from 1 (“never”) to 4 (“often”), resulting in a score between 6 and 24 points. Higher scores indicate greater loneliness.

While the original 20-item version has shown high internal consistency (Coefficient *α* = 0.96) and great validity, a large cross-cultural study with participants from Germany, Indonesia and the USA found that it did not meet criteria for measurement invariance across different cultures (47). Therefore, the 6-item version (ULS-6) was proposed as it demonstrated configural, metric, scalar and error invariance, making it a reliable instrument for cross-cultural measurement of loneliness.

##### Hospital anxiety and depression scale (HADS)

3.4.2.4

Symptoms of anxiety and depression and their severity will be assessed using the Hospital Anxiety and Depression Scale (HADS) (48). It consists of 14 items, with seven items concerning depression (HADS-D) and the other seven items concerning anxiety (HADS-A). Each statement is answered on a 4-point scale, with the self-descriptive response option varying from question to question. Possible answers inquire about the frequency or severity of symptoms or the extent of behavioral change from the past to the present. Two sum scales result that range from 0 to 21 points, with higher scores indicating more severe depression or anxiety and a cut-of ≥8 indicating clinically relevant symptoms. All items can be summed up to a total score from 0 to 42 for a global screening of mental illnesses, with a cut-off of ≥14 indicating clinically relevant mental health problems.

The validated German version has proven good internal reliability (Cronbach's *α* = 0.83 for HADS-A and 0.82 for HADS-D and 0.82−0.90 for the global scale), along with a solid content, factor and construct validity (49).

##### Trust in nurses scale—4-item version

3.4.2.5

To measure the trust of patients in their treating nursing staff, the Trust in Nurses Scale 4-item version will be applied, with four questions regarding activities of nursing staff or feelings of patients (50). These are ranked on a 6-point Likert-type scale from 1 (“never”) to 6 (“always”). Scores are summed up and higher scores indicate higher trust in nursing staff. It demonstrated good internal consistency (Coefficient *α* = 0.82) and validity with clear factor structure and excellent model fit.

The original 5-point version will not be used in this study as the additional question addresses nursing staff communicating accurate information about the patients' cancer, which does not to the present feasibility study.

At the time of protocol development, no validated German version was available. Still, trust in nursing staff as indicator for the nurse-patient-relationship represents a key research objective in this feasibility study. Therefore, the original version was translated into German, following selected steps of the cross-cultural adaption process by Beaton et al. (51). Specifically, the questionnaire was initially translated (stage 1) by the author, a native German speaker. The review by a native speaker (Stage 3) was conducted by a native English speaker of the working group to improve linguistic clarity and conceptual consistency. Additionally, the translated version was reviewed by the writers of the original protocol draft with expertise in clinical psychology, research and nursing. Accordingly, this German version should be considered a preliminary translation, as no full cross-cultural validation with back-translation (stage 2), expert committee review (stage 4) and pretesting (stage 5) were conducted.

##### Intervention diary

3.4.2.6

Moreover, a self-developed intervention diary will document session frequency and duration, whether sessions were conducted independently or with nursing staff, and any technical difficulties, interruptions or early termination. To capture immediate perceived responses to individual VR sessions with minimal participant burden, will rate their overall session experience on a 5-point scale ranging from 1 (“very unpleasant/not acceptable”) to 5 (“very pleasant/very acceptable”) and may note spontaneous impressions or notable experiences directly after the session. In addition, the overall dropout rate will be recorded.

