In the present feasibility study, the Attention Restoration Theory informs the conceptual rationale for using immersive VR-based forest exposure in long-term care. The primary goal of VR-based nature interventions is to provide visual nature experiences to long-term care residents despite mobility limitations, thereby supporting their well-being and potentially preventing outcomes such as sleep disturbances, affective disorders, loneliness, and reduced trust in nursing staff. The study focuses on feasibility, acceptability, and implementation in routine care, while exploratory questionnaire data will describe changes in sleep quality, anxiety and depressive symptoms, subjective wellbeing, loneliness, and trust in nursing staff.

Figure 1 illustrates the assumed pathways of the VR-based nature intervention. The immersive forest videos are expected to provide a restorative nature experience through soft fascination, attentional restoration, relaxation, distraction, and perceived presence. These processes may contribute to exploratory changes in sleep quality, anxiety and depressive symptoms, subjective wellbeing, and loneliness. In joint sessions with nursing staff, the shared VR experience may additionally support interpersonal connection and trust in nursing staff. The primary focus of the present study is feasibility and acceptability, including adherence, barriers and facilitators, safety, and implementation within long-term care routines.

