### Primary objective

2.1

To evaluate the feasibility and acceptability of implementing a VR-based nature intervention in long-term care facilities from the perspectives of residents and nursing staff.

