#### Quantitative data analysis

3.5.2

Changes from baseline to T1 and T2 will be analyzed using descriptive statistics such as means, standard deviations, medians, frequencies, and ranges using SPSS (54). Descriptive summaries will be presented for the total sample and, where meaningful, separately by study site to explore whether feasibility indicators, missing data, adherence, or questionnaire trends vary between the two long-term care facilities. Site-specific descriptive patterns will be interpreted cautiously and considered alongside qualitative findings on contextual factors, barriers, and facilitators.

The analysis population will include all participants with data available at each respective time point, including those who discontinue the intervention prematurely. Missing data will be reported, but no imputation will be applied due to the small sample size. Given the exploratory nature of the study, no further statistical testing is planned at this stage. Session frequency and duration, as well as dropout rates, will be analysed descriptively to assess intervention adherence. Session ratings and spontaneous comments documented in the intervention diary will be analyzed descriptively and used to complement the qualitative interview data on acceptability, perceived short-term responses, and implementation feasibility.

No comparator is included in this feasibility study as the primary aim is to explore the feasibility of VR-based nature interventions in long-term care settings and not the efficacy. As this is a feasibility study with a small, exploratory sample size, no minimal important change is defined for individual participants and continuous outcome data will not be dichotomized or categorized for inferential analysis. Additionally, no composite outcomes are included in this study.

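### The diary's session rating, the only direct numeric rating of acceptability, merges pleasantness and acceptability on one scale, so its score cannot be attributed to either

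*Protocol article*

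**What the plan says.** Section 3.4.2.6 of the protocol article describes a diary that the study team developed itself. Besides session logistics it contains one rating, given directly after the session, on a "5-point scale ranging from 1 (“very unpleasant/not acceptable”) to 5 (“very pleasant/very acceptable". The stated aim is to record the immediate response to each session at little burden. As printed, the sentence has no grammatical subject: "with minimal participant burden, will rate their overall session experience".

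Section 3.5.2 (Quantitative data analysis) says that the ratings and the spontaneous comments will be summarised descriptively and "used to complement the qualitative interview data on acceptability, perceived short-term responses, and implementation feasibility".

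The primary objective in section 2.1 is "To evaluate the feasibility and acceptability of implementing a VR-based nature intervention in long-term care facilities", so acceptability belongs to the main question of the study. The Abstract assigns the primary outcome to semi-structured interviews and content analysis. Section 3.4.1 places those interviews at T2, after the intervention has ended.

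**The concern.** Pleasantness and acceptability can differ. A resident may enjoy the forest and still find the headset or the bedtime slot too much trouble. Another may find the video dull and be quite willing to have it again. With both words at each end of one scale, the respondent has to decide which question to answer or strike a compromise, and the diary does not record which was done.

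Section 3.5.2 names acceptability and short-term responses as separate subjects to be informed by the rating. Pleasantness is a short-term response. One merged number cannot inform both. At stake is the descriptive value of the only session-by-session number that bears directly on acceptability, and how well it can be set against interview themes.

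**Working it through.** The point concerns the wording of an item. The plan states no figure to reproduce, so the check is mainly a reading of the relevant sections side by side.

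**1. What the scale can express.** Only the two ends are labelled in the article.

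| Session was | Acceptable | Not acceptable |
|---|---|---|
| Pleasant | upper end (5) | no defined place |
| Unpleasant | no defined place | lower end (1) |

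Two of the four combinations have no defined answer. Read backwards, a middle score may mean that both judgements were middling, or that one was high and the other low. A score of 5 may come from someone who answered only one half. The anchors are also not mirror images: the acceptability half runs from absence (not acceptable) to a high degree (very acceptable), whereas the pleasantness half runs between two extremes.

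**2. Whether another number covers acceptability.**

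- The standardised questionnaires in section 3.4.2 are given "to assess sleep quality, anxiety and depressive symptoms, psychological well-being, loneliness, and trust in nursing staff". None of these is acceptability.
- The other diary data are assigned elsewhere: "Session frequency and duration, as well as dropout rates, will be analysed descriptively to assess intervention adherence".
- The Introduction, however, describes the focus as "feasibility and acceptability, including adherence, barriers and facilitators, safety, and implementation within long-term care routines". Adherence can therefore serve as an indirect numeric indicator.

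The diary item is thus the only *direct* numeric rating of acceptability, but not the only number that bears on it.

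**3. How many ratings are involved.** Inputs: 10 residents (section 3.3) and three sessions a week for four weeks (section 3.2).

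- Sessions per resident: 3 x 4 = 12.
- Ratings if every session is completed and rated by the resident: 10 x 12 = 120.

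All of them use the merged anchors.

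**4. Whether a shift in the mean can be computed.** Let *a* be the share of sessions in which pleasantness would score above acceptability, *b* the share in which it would score below, and *d* the average gap in either case. The two means then differ by (*a* - *b*) x *d*. The documents give none of the three quantities. If *a* = *b* the difference is 0, although the individual scores remain ambiguous. No figure can be defended, and the point does not need one.

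**5. Who rates.** "will rate their overall session experience on a 5-point scale" follows directly on the phrase about burden, with no subject. Section 3.3 counts both residents and staff as participants, and in joint sessions the staff member also wears a headset. Section 3.4.2 opens with residents completing the questionnaires, and section 3.2 describes an individual diary that notes whether staff were present. Both favour the resident as rater. A dropped word is the likeliest explanation.

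**6. Use in integration.** Section 3.5.3 looks for convergence, complementarity and divergence between the two strands. A number without a single meaning cannot clearly agree or disagree with an interview theme on acceptability.

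**The case against.** The strongest reply is that the item is a global impression. It asks about the session as a whole, its stated purpose is the immediate response, and the slash may only paraphrase the good and bad ends of one overall judgement. Acceptability in routine care is explored in the interviews. Comments and documented reasons for missed or incomplete sessions would show many of the cases in which liking and acceptance part.

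Much of this stands. The rating is supplementary, it is read together with comments, and it is never the sole basis for a conclusion. Two things remain. Section 3.5.2 does put the rating to use for acceptability, so the protocol asks more of it than a general impression. The comments are optional, so they cannot be relied on to separate the two meanings afterwards.

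A reader might infer three stronger points that the documents do not support:

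- *That decisions about the later RCT turn on this mean.* Section 3.5.3 sets no progression criteria and gives qualitative feedback priority over the numbers.
- *That acceptability has no other numeric evidence.* Adherence and dropout are indirect evidence, as shown above.
- *That the mean is biased by a definite amount.* Any such figure needs an assumed rate of disagreement and an assumption that all of it runs one way. With mixed directions the shift may be nil.

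**Conclusion.** The concern holds in a limited form. The item is double-barrelled on its face, and the article prints the anchors themselves, so this is not a detail left to a fuller document. Every rating, up to 120 with full completion by residents, is affected in the sense that it cannot be attributed to one construct.

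The loss is in descriptive value and in comparison with the interviews. It does not threaten the primary outcome, which is qualitative, and no threshold or test depends on the score. The conclusion rests on one assumption: that pleasantness and acceptability differ in at least some sessions. The protocol's own separation of acceptability from short-term responses makes that reasonable. The change is worth making because it is cheap and because merged ratings cannot be separated later. The missing rater is a minor clarification.

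**What to change.** Replace the single rating with two 5-point items, reported separately:

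- pleasantness, from *very unpleasant* to *very pleasant*;
- acceptability, from *not at all acceptable* to *fully acceptable*.

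In section 3.5.2, say which item informs acceptability and which informs short-term responses. Restore the subject of the sentence so that the rater is named. If staff also rate joint sessions, record and report their ratings apart from those of residents.

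A single item with acceptability anchors only would add no burden, but it would lose the immediate experience that the item is meant to capture, so two items are preferable.

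The cost is one extra tick per session: 12 per resident, or 10 x 12 = 120 in all. The diary is self-developed, so no validated instrument is altered. Section 5.1 sends significant changes to data collection to the ethics committee before implementation and updates the registration for relevant changes, so the revision may need that step. If diaries are already in use, summarise ratings made on the old anchors separately from those on the new ones.

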### Data analysis

3.5

#### Qualitative data analysis

3.5.1

Data from interviews will be analysed with an inductive-deductive qualitative content analysis based on Kuckartz & Rädiker (52). Data will be managed and analysed with the qualitative data analysis software MAXQDA 24 (53). This allows for the structured development of categories to identify themes relevant to participants in terms of feasibility, acceptability and preliminary effects.

#### Quantitative data analysis

3.5.2

Changes from baseline to T1 and T2 will be analyzed using descriptive statistics such as means, standard deviations, medians, frequencies, and ranges using SPSS (54). Descriptive summaries will be presented for the total sample and, where meaningful, separately by study site to explore whether feasibility indicators, missing data, adherence, or questionnaire trends vary between the two long-term care facilities. Site-specific descriptive patterns will be interpreted cautiously and considered alongside qualitative findings on contextual factors, barriers, and facilitators.

The analysis population will include all participants with data available at each respective time point, including those who discontinue the intervention prematurely. Missing data will be reported, but no imputation will be applied due to the small sample size. Given the exploratory nature of the study, no further statistical testing is planned at this stage. Session frequency and duration, as well as dropout rates, will be analysed descriptively to assess intervention adherence. Session ratings and spontaneous comments documented in the intervention diary will be analyzed descriptively and used to complement the qualitative interview data on acceptability, perceived short-term responses, and implementation feasibility.

No comparator is included in this feasibility study as the primary aim is to explore the feasibility of VR-based nature interventions in long-term care settings and not the efficacy. As this is a feasibility study with a small, exploratory sample size, no minimal important change is defined for individual participants and continuous outcome data will not be dichotomized or categorized for inferential analysis. Additionally, no composite outcomes are included in this study.

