**Methods:**

Ten residents and ten nursing staff members from two long-term care facilities complete twelve 15-minute virtual reality sessions using a 360° forest video developed by the study team. Over four weeks, residents conduct three sessions each week. Six residents receive support by nursing staff once weekly. The primary outcome feasibility will be qualitatively assessed through semi-structured interviews and qualitative content analysis. Secondary outcomes, including sleep quality, anxiety, depressive symptoms, wellbeing, loneliness and trust in nursing staff, will be analysed using quantitative descriptive analysis.

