### Secondary objectives

2.2

To identify barriers to implementation from the perspectives of residents and nursing staff.To assess changes in the nurse-patient relationships resulting from joint sessions.To explore potential effects of the intervention on sleep quality, mood, subjective well-being, feelings of loneliness among residents, and trust in nursing staff.

These outcomes address challenges that are especially common among long-term care residents and have previously been shown to benefit from nature-based interventions in prior studies (18, 20).

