Five out of 10 residents will complete one VR session per week together with a member of the nursing staff^1^. The participating staff member may vary between sessions depending on shift schedules, workload, and availability. This approach reflects real-world long-term care routines, where residents are commonly supported by several members of the nursing team. Accordingly, trust is conceptualized as residents' perceived trust in nursing staff more broadly. The qualitative interviews will explore how residents and nursing staff perceive the joint sessions, including whether shared VR experiences influence interpersonal connection, perceived support, and trust in nursing staff under routine care conditions.

The remaining four residents will conduct the sessions independently following an initial briefing and instructions from nursing staff. Residents receive a personal VR headset for the duration of the intervention and complete the sessions before bedtime in an upright position in bed or another seated position.

The VR system is preconfigured to minimise handling steps. Specifically, the VR headsets will be fully configured by the research team before use. Residents are not expected to navigate the standard Meta Quest menu or select videos independently. Instead, the respective intervention video will be preselected and started by nursing staff after instruction. Thus, residents only need to wear the headset and experience the video, while technical handling is kept to a minimum. For joint sessions, nursing staff will use shared VR headsets, which require a short calibration phase before each session.

At the beginning of the intervention period, an information session with hands-on training is held with participating residents and nursing staff to explain the use of the VR headsets, outline the course of the intervention, and address any questions. Usual care and daily routines within the long-term care facilities, regular medication, therapeutic procedures and social activities may continue unchanged during the intervention period.

After each use, the VR headsets and contact surfaces will be cleaned and disinfected according to the facility's hygiene standards.

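### Questionnaire and adherence data are summarised in total and by site but not by session format, so the trust trend compared with the interviews mixes residents with and without planned joint sessions

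*Protocol article*

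**What the plan says.** Secondary objectives (2.2) include: "To assess changes in the nurse-patient relationships resulting from joint sessions". The same section lists trust in nursing staff separately, among the outcomes whose potential effects are to be explored.

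Section 3.3 says "residents will be assigned into two groups, aiming for an equal distribution of characteristics": one with a weekly session shared with a nurse, one without. It adds that "variation between individual and joint sessions with nursing staff allows the exploration of contextual variability".

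The Introduction's account of the conceptual framework places the trust pathway in the joint sessions. Section 3.4.2.5 says that "trust in nursing staff as indicator for the nurse-patient-relationship represents a key research objective in this feasibility study". All residents are to complete the questionnaires at T0, T1 and T2 (3.4.2).

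On analysis, section 3.5.2 says: "Descriptive summaries will be presented for the total sample and, where meaningful, separately by study site". It names site as the factor across which feasibility indicators, missing data, adherence and questionnaire trends are explored. Session format is not named. Section 3.5.3 then compares questionnaire trends, trust included, with the interview material.

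The group sizes conflict. The Abstract says "Six residents receive support by nursing staff once weekly". Section 3.2 says "Five out of 10 residents will complete one VR session per week together with a member of the nursing staff", and then "The remaining four residents will conduct the sessions independently following an initial briefing and instructions from nursing staff".

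**The concern.** The plan forms two groups, tries to balance them, and expects trust to respond mainly in one of them, but its numerical summaries never show them apart. The one breakdown it names, by site, cannot stand in for format, since nothing in the article says that site and session format coincide.

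What is at stake is the convergent comparison. Interview accounts of shared sessions would be set beside a trust trend in which 40-50% of the residents have no planned joint session. The two strands could seem to diverge because a change in the joint group was averaged down. They could also seem to converge because everyone changed for some unrelated reason. Either reading would feed into the design of the later RCT.

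Two smaller points follow. Section 3 promises to analyse whether residents can run sessions independently; adherence and session ratings by format bear directly on that, and section 3.5.2 does not provide them. And the words of objective 2.2 attribute change to the joint sessions, which an unrandomised split of about ten residents cannot support.

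**Working it through.** The plan gives no sample size calculation, standard deviation or target change, so there is no figure of its own to reproduce. The check has three parts.

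**1. Share of residents with a planned joint session (f).** The counts come from the Abstract and section 3.2.
- Six of ten: f = 6/10 = 0.60. With the four independent residents of section 3.2, 6 + 4 = 10.
- Five of ten: f = 5/10 = 0.50. Section 3.2 then names only four others, and 5 + 4 = 9.
- Five of the nine accounted for: f = 5/9 = 0.56.

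So 40-50% of the residents in the pooled trust summary have no planned joint session.

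**2. What the pooled mean shows.** With complete data,

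pooled change = f × D_joint + (1 − f) × D_indep.

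If D_indep = 0, the pooled change is f × D_joint, that is 0.60, 0.56 or 0.50 of the joint-group change.

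For illustration, take an assumed D_joint of 2 points. The trust scale has four items scored 1 to 6, so its sum runs from 4 × 1 = 4 to 4 × 6 = 24.

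| Assumed D_indep | f = 0.60 | f = 0.56 (5/9) | f = 0.50 |
|---|---|---|---|
| 0 | 1.20 | 1.11 | 1.00 |
| 0.5 | 1.40 | 1.33 | 1.25 |
| 1.0 | 1.60 | 1.56 | 1.50 |

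The pooled figure is also ambiguous. At f = 0.50, a pooled change of 1.0 arises from 2 points in the joint group and none in the other (0.5 × 2 + 0.5 × 0). It arises equally from 1 point in both groups (0.5 × 1 + 0.5 × 1). The first pattern fits a role for joint sessions and the second does not, and the planned summary cannot tell them apart.

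**3. What a split could deliver.** The 95% half-width of a between-format difference, in units of the SD of the change, is t(0.975, n1 + n2 − 2) × √(1/n1 + 1/n2).
- 6 v 4: 2.306 × √(1/6 + 1/4) = 1.49 SD.
- 5 v 4: 2.365 × √(1/5 + 1/4) = 1.59 SD.
- 5 v 5 (not stated anywhere, shown only for reference): 2.306 × √(1/5 + 1/5) = 1.46 SD.

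A split can show patterns in individual residents. It cannot estimate a format effect with useful precision.

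**The case against.** The strongest reply is that the plan never asks the questionnaire to answer the joint-session objective. Section 2.3 makes the nurse-patient relationship a qualitative research question. Its quantitative question is only whether descriptive changes, trust included, occur over the course of the intervention, and a total-sample summary answers that. Sections 3.2 and 3.4.1 have the interviews explore the joint sessions, the relationship and trust with residents and staff. All of this stands. A reader might infer that the objective is left unanswered or that the pooled summary is wrong for its own question; the documents support neither.

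A reader might also infer that trust will be understated by 40-50%. That requires no change at all in the independent residents. Section 3.2 has staff brief them, start their videos and support the session after a missed one, and it defines trust as trust in nursing staff in general. Their change may well not be zero, so the dilution is conditional.

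It can further be said that there is no comparator and that the cells are tiny. That is a sound reason against testing. It is a weak reason against a descriptive display, since the plan already accepts a site split of the same ten residents.

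Finally, table layouts are often left to a fuller document. But section 3.5.2 does name its breakdowns and their purpose, and session format, which the diary already records, is not among them.

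**Conclusion.** The point holds as a modest, inexpensive improvement to the quantitative strand and its integration with the interviews. It is not a flaw in the study's main question. As written, the trust trend entering the convergent comparison pools residents with and without planned joint sessions. A change confined to the joint group would show at 50-60% of its size, assuming no change in the independent group and complete data. If the independent residents also change, the shortfall is smaller, but the pooled mean still cannot show whether the two groups differ.

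Nor would the split show what joint sessions cause. The groups are not randomised, contain about four to six residents each, and would give a half-width of about 1.5 SD for a difference. The causal phrasing in objective 2.2 therefore goes beyond the design with or without the split.

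**What to change.** 1. Reconcile the group sizes between the Abstract and section 3.2. Until that is done, the breakdown has no defined groups.
2. In section 3.5.2, add session format as assigned as a planned descriptive breakdown for trust, session ratings and adherence. Individual T0-T1-T2 trajectories, marked by format and site, are preferable to group means at these numbers.
3. As a supplement, report from the intervention diary how many sessions each resident actually held jointly. Delivered format may differ from assigned format, for instance after a missed session.
4. Use the same split in the convergent comparison of section 3.5.3, so that accounts of joint sessions are set beside the trust data of the residents who were assigned them.
5. Reword the objective in section 2.2 along the lines of: *describe changes in the nurse-patient relationship in residents with and without joint sessions*.

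The cost is a few extra tables and plots from data already collected. The downside is that cells of about four to six unrandomised residents invite over-reading, so the display must be labelled descriptive only, with no test and no claim of a format effect.
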